It was not possible to collect sufficiently valid consumption data in the ED setting to assess alcohol consumption levels based on consumption owing to interview time constraints. Instead, we defined hazardous, harmful and dependent alcohol consumption using scores from the Fast Alcohol Screening Test (FAST).^72^ The use of FAST to identify alcohol misuse (ie, hazardous, harmful and dependent alcohol consumption) has been supported by national guidelines for the prevention of harmful drinking.^73^ Derived from the AUDIT^74^ the four item FAST was specifically developed and validated within ED as it is quick to administer and less disruptive in the busy ED setting.^72 75^ The FAST has been found to be the most sensitive and accurate short alcohol screening tool commonly administered to identify alcohol misuse in adults attending ED.^76 77^ and has been used in a number of clinical studies.^78 79^ A score of ≥3 on the FAST indicates hazardous drinking. We are undertaking a parallel examination of The FAST screening tool to further discriminate alcohol use disorders in ED attendees. In our study MUP is theorised to reduce alcohol misuse (hazardous, harmful and dependent alcohol consumption), so reducing both acute and chronic alcohol-related harm, and therefore the numbers of alcohol-related attendances at both EDs and at SHCs. Hazardous drinkers are expected to be more likely than harmful or dependent drinkers to present with acute harms (such as injuries and assaults), while harmful/dependent drinkers are likely to present with both acute conditions and acute consequences of chronic conditions (such as pancreatitis and gastritis). Therefore there may be an early impact on ED attendances relating to chronic as well as acute alcohol-related conditions.

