## Methods and analysis

### Component 1: audit of alcohol-related attendances at EDs

#### Study design

This component is designed to quantify changes in alcohol-related attendances at ED settings as a result of MUP. The FAST is used to identify alcohol misuse in the ED. The component focuses on answering research aim (RA)1, namely:What are the impacts of MUP for alcohol on alcohol-related harms and drinking patterns (using the FAST) for ED attendees and by subgroups of interest (age, sex and deprivation)?Does the effect of MUP vary dependent on the type of alcohol-related harm:Acute alcohol-related harms vs chronic alcohol-related harms?Broad diagnostic groups (based on coding systems used in EDs?
Does MUP affect alcohol consumption (on the basis of the FAST^72^ score and alcohol misuse over the reporting period among people attending EDs (FAST >3)?Does the MUP intervention effect size (assessed on a variety of measures including FAST) vary at the second and third time points?

Lower level outcomes are set out in the Data collection section. To answer RA1, a natural experiment design employing a repeated cross-sectional audit of all alcohol-related attendances at EDs in two Scottish hospitals and two North of England comparator hospitals at three time points was most appropriate to assess causality. A Randomised Controlled Trial was not feasible. The study methods and tools were based on previous studies used to quantify the national prevalence of alcohol-related attendances in EDs in England^79^ and informed by the experience of the Scottish ED Alcohol Audit, carried out across 15–20 hospitals throughout mainland Scotland between October 2005 and June 2007.^80^

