#### Outcome measures

The primary outcome will be the proportion of attendances that are alcohol-related, using a composite measure which defined the attendance as alcohol-related if any one (or more) of the following was true:patient self-reports attendance is alcohol-related;patient reports alcohol consumption in past 24 hours >8 units in men, >6 units in women; orpatient not approached or interview terminated because too intoxicated with alcohol.

Secondary outcomes will be:the absolute number and proportion of alcohol-related attendances;alcohol misuse defined by the FAST score >3;mean FAST score by age, gender and deprivation;prevalence of binge drinking in the past week, andself-reported reason for attendance.

Outcomes will be compared between intervention and control areas, adjusted for baseline attendances.

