#### Power calculation

Based on the experience of the 24 hours audit of EDs in England,^79^ and assuming that we would be able to recruit 50% of eligible ED attendees, we anticipated that the four sites (two Scotland, two England) would result in 940 recruits per week. Recruiting over 3 weeks pre-implementation and post-implementation—giving a total sample size of 5640 for the baseline and any one subsequent wave—would mean that we would be highly powered (>80%) to detect an effect size of ±5% in the proportion of alcohol-related attendances from an estimated 30% with 95% significance. We have used a base rate of 30% informed by the 24 hours audit of EDs in England^79^ and assumed a 5% decrease would be of public health importance and may be expected based on current evidence.^79^ For subgroup analyses, we would have good power (>80%) to detect an effect size of 0.23 on the FAST score among those from the most deprived quintile (estimated to be 25% of attendances) and an effect size of 0.27 among those aged 18–24 years (estimated to be 15% of attendances).

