#### Outcome measures

The primary outcome from component 2, which aims to reveal unintended effects, will be the proportion of patients self-reporting psychoactive substance use other than alcohol in the last month. Secondary outcomes will be drug-specific rates of use within the last month, sources of alcohol purchase (including cross-border, internet, smuggled or moonshine), rates of higher risk drinking (as measured by FAST score>3), self-reported binge-drinking and analyses for differential displacement of use of illicit psychoactive drugs (including age, gender, highest achieved education, problematic drinkers)

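### The Introduction puts hazardous drinking, and so alcohol misuse, at FAST 3 or more, but the dichotomised FAST outcomes use more than 3, so respondents scoring exactly 3 become non-cases

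*Protocol article*

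**What the plan says.** All the relevant text is in the protocol article.

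- **Introduction, paragraph on FAST.** The categories come from the instrument: "we defined hazardous, harmful and dependent alcohol consumption using scores from the Fast Alcohol Screening Test (FAST". Misuse includes the hazardous category: "The use of FAST to identify alcohol misuse (ie, hazardous, harmful and dependent alcohol consumption) has been supported by national guidelines". The threshold is explicit: "A score of ≥3 on the FAST indicates hazardous drinking".
- **Component 1, Study design.** One research question asks about "alcohol misuse over the reporting period among people attending EDs (FAST >3".
- **Component 1, Outcome measures.** A secondary outcome is "alcohol misuse defined by the FAST score >3". Another is "mean FAST score by age, gender and deprivation", which has no cut-off.
- **Component 2, Outcome measures.** A secondary outcome is "rates of higher risk drinking (as measured by FAST score>3".
- **Component 1, Power calculation.** The FAST statements concern the score itself, for example "good power (>80%) to detect an effect size of 0.23 on the FAST score among those from the most deprived quintile".

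No section gives a reason for a cut-off stricter than the one in the Introduction. The Research questions section says that data collection is complete and analysis has yet to begin.

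**The concern.** The article fixes the boundary of alcohol misuse in two incompatible ways. An analyst who codes the outcome as listed gets a different set of cases from one who follows the definition in the Introduction.

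FAST-based misuse is a named research question in Component 1. The Introduction also makes a fall in misuse, hazardous drinking included, the step through which minimum unit pricing is expected to reduce harm. Under the strict cut-off, part of the group that the Introduction calls hazardous drinkers is reported as not misusing alcohol. Prevalence could not be compared with results that use the stated threshold. While both cut-offs stand, the choice could also be made after results are seen, in an evaluation that will inform whether the policy continues.

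**Working it through.** No stated sample size or power figure depends on the cut-off, so there is none to reproduce. The check is a comparison of the text, followed by an illustration of size.

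**Step 1: the definitions side by side.**

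| Section | Label | Rule |
|---|---|---|
| Introduction | hazardous drinking, a part of alcohol misuse | FAST ≥ 3 |
| Component 1, Study design | alcohol misuse | FAST > 3 |
| Component 1, Outcome measures | alcohol misuse | FAST > 3 |
| Component 2, Outcome measures | higher risk drinking | FAST > 3 |

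**Step 2: who is affected.** The two rules differ only at a score of exactly 3. In the Introduction, 3 is hazardous and hazardous is misuse, so 3 is a case. Under the other three rules, 3 is a non-case.

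**Step 3: effect on prevalence and on the contrast.** In any country and wave,

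P(FAST ≥ 3) = P(FAST > 3) + P(FAST = 3).

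The strict rule therefore cannot give a higher prevalence, and gives a lower one if anyone scores 3. Taking the change from baseline in Scotland minus that in England (DiD), on the scale of proportions,

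DiD(≥ 3) = DiD(> 3) + DiD(= 3).

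The two contrasts differ only by the differential change in the share scoring exactly 3. The documents give nothing on its sign or size. Because the same rule is applied in both countries and at every wave, the contrast based on > 3 is a valid contrast of a slightly different quantity.

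**Step 4: illustrative size.** Component 1, Power calculation, expects 940 recruits per week for 3 weeks: 940 × 3 = 2820 per wave. The share scoring exactly 3 is not given, so it is assumed here.

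| Assumed share scoring 3 | Reclassified of 2820 |
|---|---|
| 2% | 2820 × 0.02 ≈ 56 |
| 5% | 2820 × 0.05 = 141 |
| 8% | 2820 × 0.08 ≈ 226 |

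Component 2, Power calculation, gives 288 per clinic per week: 288 × 6 clinics × 3 weeks = 5184 per wave. The same 2% to 8% is about 104 to 415 respondents.

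**Step 5: what does not depend on the cut-off.**

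- The Component 1 primary outcome is a composite of self-report, recent units drunk and intoxication. The Component 2 primary outcome is use of other psychoactive substances. Neither is defined by FAST.
- Mean FAST score has no threshold.
- The FAST power statements use effect sizes on the score, so no cut-off enters them.

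**The case against.** The strongest reply is that this is a small inconsistency of notation in secondary outcomes. The strict form appears three times and the inclusive form once, so the documents do not show which was intended for the outcomes. Any cut-off also hides some change: ≥ 3 does not register a shift from 4 to 3, just as > 3 does not register one from 3 to 2. In Component 1, the mean FAST score would still pick up either shift.

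Much of this stands, and it limits the point. It does not remove it. The article states both rules, so this is a contradiction and not a detail left to a fuller document. A fault in reading the PDF is unlikely, since the ≥ sign survives in the Introduction and the strict sign recurs in three places.

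A reader might infer more than the text supports:

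- **That every FAST outcome is affected.** Mean FAST score is not.
- **That the contradiction is equally direct in both components.** Component 2 labels its outcome higher risk drinking, a term that the Introduction does not define. Component 2 does list changes in alcohol misuse among its aims, so the mismatch is likely there, but the direct conflict is in Component 1.
- **That the subgroup of problematic drinkers in Component 2 is wrongly defined.** The article gives no cut-off for that group, so there is no stated rule to be wrong, and its definition may lie in a fuller document.
- **That the policy contrast is biased.** One rule applied to both countries and all waves does not by itself bias it.

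**Conclusion.** The concern holds for the dichotomised FAST measures. By the protocol's own definition, a score of exactly 3 is alcohol misuse, yet the Component 1 research question and secondary outcome exclude it. Component 2 very likely has the same mismatch under another label. As written, the rule understates misuse prevalence if anyone scores 3, changes which drinkers the outcome captures and breaks comparability with the stated threshold.

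The size in people rests entirely on the assumed share scoring 3 and on the planned recruitment. The contradiction does not depend on those figures. Severity is should-fix, not must-fix, because only secondary outcomes and the related research question are touched.

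**What to change.** Before analysis starts, reconcile the Introduction, Component 1 Study design, Component 1 Outcome measures and Component 2 Outcome measures to one FAST cut-off.

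- If the outcome is to measure alcohol misuse as the Introduction defines it, the cut-off is 3 or more.
- If more than 3 was intended, give the reason and relabel the outcome so that it is not called alcohol misuse.
- In either case, the other cut-off can be reported as a sensitivity analysis.

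The cost is a few words of text and one line of code. No data need to be collected again, because the FAST scores themselves do not change. The choice should be recorded before any result by country is seen.

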#### Study population

People aged 16 years and over attending EDs during data collection periods were approached. The study monitored, but excluded from interview:those acutely physically or mentally ill such that informed consent or full participation was impossible to obtain (including gross intoxication),those with whom it was impossible to adequately communicate (eg, patients unable to speak English despite the use of an interpreter where available), andthose who left the department before an approach was made or who were deemed by the research nurses as too threatening to approach.

Reasons for not approaching were recorded to address potential selection bias.

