#### Data collection

Baseline data collection took place in February 2018 prior to the implementation of MUP on 1 st May 2018. The second and third waves of data collection took place approximately 8 and 12 months post baseline and 5 and 9 months post implementation, with care taken to avoid the inclusion of specific events that are expected to be associated with increased or decreased alcohol consumption, for example local holidays were checked to avoid differences between groups. Each wave collected data over 3 weeks, and to maximise collection of both alcohol-related attendances and alcohol misuse, data collection occurred from 20:00 to 03:30 from Thursday to Sunday (ie, 30 hours per week during this time period) and 09:00 to 16:30 from Monday to Wednesday (ie, 22.5 hours per week during this time period).

During study data collection periods, patients were approached by a research nurse to seek permission to complete a short face-to-face interview. All eligible patients were approached, informed consent obtained and a face-to-face interview based on a previously used patient questionnaire was administered electronically using a tablet (iPad).^78^ An ED attendance database was maintained for all attendances during data collection periods to allow monitoring of patient recruitment.

The interview collected details on the following:basic demographic information (age; gender; ethnicity; marital, employment and housing status (including unstable housing status such as no fixed abode and hostel accommodation); postcode sector);attendance details (date and time, triage category, time and date of incident);how much alcohol was consumed in the past 24 hours;date, time and place of last drink;the largest number of drinks on any 1 day in the previous week;self-reported reason for attendance, such as assault, collapse etc;alcohol misuse in the past year (as assessed by the FAST)^72^ andwhether alcohol consumption changed over the previous 12 months.

In addition we asked whether interviewees thought their current ED attendance was related to their or someone else’s drinking, and how many times they had attended any ED in the previous 12 months.

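### Component 1 measures binge drinking and FAST misuse in interviewees only, so a fall in gross intoxication under MUP would, by this route alone, leave recorded binge prevalence unchanged or raise it slightly

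*Protocol article*

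**What the plan says.** All references are to the protocol article, Component 1.

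- **Outcome measures.** The secondary outcomes include "prevalence of binge drinking in the past week" and "alcohol misuse defined by the FAST score >3", together with mean FAST score. No denominator is given for any of them, and nothing is said about attendees who could not be interviewed.
- **Data collection.** Both measures are interview items. The list that opens with "The interview collected details on the following" contains "the largest number of drinks on any 1 day in the previous week" and "alcohol misuse in the past year (as assessed by the FAST").
- **Study population.** Attendees are monitored but not interviewed if they are so ill that "informed consent or full participation was impossible to obtain (including gross intoxication").
- **Outcome measures, primary outcome.** An attendance counts as alcohol-related if the patient was not approached, or the interview was stopped, because of intoxication with alcohol. The primary outcome therefore includes the people whom the interview leaves out.
- **Mitigation.** "Reasons for not approaching were recorded to address potential selection bias". The strengths and limitations box gives differential selection of intoxicated attendees as an example of the main limitation. Data collection also describes aggregate age, sex and diagnosis data on all attendees, but these carry no drinking information.

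**The concern.** Selection into the interview depends on how drunk the attendee is, and MUP is meant to change that. The Introduction theorises that MUP reduces hazardous, harmful and dependent drinking, so fewer attendees too drunk to interview is a plausible sign of success. Two things can then happen to them:

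- They no longer attend. They were never in the interview data, so recorded binge prevalence does not move although prevalence among all attendees falls.
- They attend less intoxicated and can be interviewed. They enter the data mostly as binge-positive, and recorded prevalence rises.

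A change confined to Scotland would not cancel against England. Research aim 1 covers drinking patterns as well as harms, and the Introduction lists a move from regular to binge drinking among the risks that the ED and clinic studies will address. A small artefactual rise, or a masked fall, in past-week binge prevalence bears on that question and feeds into evidence for the sunset-clause decision.

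**Working it through.** **Planned size.** The Power calculation section gives 940 recruits per week over 3 weeks in each of two waves: 940 × 3 × 2 = 5640, as stated. With an equal split between countries (assumed), that is 940 × 3 / 2 = 1410 per country per wave. The article gives no figure for the share too intoxicated or for binge prevalence, so what follows is an illustration.

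**Assumed inputs.**
- q0 = 5% of attendances too intoxicated at baseline; q1 = 4% or 3% after MUP
- b = 30% binge prevalence among interviewable attendees, with their own drinking held fixed
- s = share of the newly interviewable who are binge-positive, 1.0 or 0.8
- everyone too intoxicated counts as having binged in the past week

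**Baseline.** Recorded 30.0%. All attendees: 0.05 + 0.95 × 0.30 = 33.5%.

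**They become interviewable.** Recorded = [(1 − q0)b + (q0 − q1)s] / (1 − q1); all attendees = q1 + (1 − q1) × recorded.

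| s | q1 | Recorded | All attendees |
|---|---|---|---|
| 1.0 | 4% | 0.295/0.96 = 30.7% | 33.5% |
| 1.0 | 3% | 0.305/0.97 = 31.4% | 33.5% |
| 0.8 | 4% | 0.293/0.96 = 30.5% | 33.3% |
| 0.8 | 3% | 0.301/0.97 = 31.0% | 33.1% |

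The recorded figure rises by 0.5 to 1.4 points while the all-attendee figure is flat or falling.

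**They stop attending.** Recorded stays at 30.0%. All attendees = [q1 + (1 − q0)b] / [1 − (q0 − q1)] = 0.325/0.99 = 32.8%, or 0.315/0.98 = 32.1%.

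**Wider range.** Take 2–10% too intoxicated, 25–50% prevalence in interviewees, 90% positive among the too intoxicated, and a 25–50% fall in their number. The recorded change is then 0.0 points under non-attendance and +0.2 to +3.4 points if they become interviewable. It is never negative while the excluded are positive more often than interviewees.

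**Offset by a real fall among interviewees.** The rise is cancelled if prevalence among those already interviewable falls by (q0 − q1)(s − b)/(1 − q0). In the main illustration this runs from 0.01 × 0.5/0.95 = 0.5 points to 0.02 × 0.7/0.95 = 1.5 points.

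**Against sampling error.** At 30% with 1410 per cell, ignoring clustering, the standard error of a one-wave country difference is √(2 × 0.21/1410) = 1.7 points, and of a difference in differences √(4 × 0.21/1410) = 2.4 points.

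**Adding the excluded back without weighting.** The Power calculation section assumes that 50% of eligible attendees are recruited, whereas too-intoxicated attendees can all be counted from the attendance log. Per 100 attendances, with s = 1:
- Baseline: (5 + 0.5 × 28.5)/(5 + 0.5 × 95) = 19.25/52.5 = 36.7%
- Two points moved: (3 + 0.5 × 30.5)/(3 + 0.5 × 97) = 18.25/51.5 = 35.4%

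That is a fall of 1.2 points with the true value fixed at 33.5%. Moving one point gives (4 + 0.5 × 29.5)/(4 + 0.5 × 96) = 18.75/52 = 36.1%, a fall of 0.6 points.

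**With interviewees weighted by 1/0.5.** Baseline (5 + 28.5)/(5 + 95) = 33.5%; two points moved (3 + 30.5)/(3 + 97) = 33.5%. The artefact disappears.

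**The case against.** The strongest points on the other side are these.

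- **The net direction is open.** A reader might infer that, if MUP works, recorded binge drinking and misuse must stay flat or rise. The documents do not support that. MUP is theorised to reduce problem drinking generally, and in the main illustration a fall of 0.5 to 1.5 points among those already interviewable is enough to cancel the rise. This stands.
- **The size is assumed and small.** No input is in the article, and 0.5 to 1.4 points is below one standard error at the planned size. Only the upper part of the wider assumed range exceeds it. This stands: on its own the pathway is unlikely to produce an apparent shift to binge drinking.
- **FAST is not demonstrated.** A reader might extend the binge result to FAST misuse. FAST covers the past year, and one intoxicated attendance does not establish a score above the cut-off. This stands.
- **The selection problem is disclosed, and an article may leave secondary-outcome detail to the full plan.** This stands in part. The disclosure is general, and logging reasons is not an analysis rule. The article itself fixes the handling for the primary outcome and lists these outcomes beside it without one.
- **Component 2 also measures FAST and binge drinking, without listing intoxication as an exclusion.** True, but in sexual health clinic patients. It does not answer the question for ED attendees.
- **Simply recoding the excluded as positive introduces its own bias.** This stands, and it shapes the fix.

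**Conclusion.** The point holds as a statement about one selection pathway. Past-week binge drinking and FAST misuse describe interviewable attendees only, while the primary composite includes those too intoxicated to interview. A Scotland-only fall in gross intoxication would, by this route alone, contribute no change or a rise of about 0.5 to 1.4 points in recorded binge prevalence. That rests on the assumed 5% too intoxicated, 30% binge prevalence, and a move of one to two points of attendances. The bias is against detecting benefit. The net direction depends on what happens among interviewees, and for FAST the effect is plausible but not shown. The primary outcome is not affected in this way. The matter is worth settling before analysis, which the Research questions section says had not yet begun.

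**What to change.** 1. Keep the interview-only results for binge drinking and FAST misuse, and label them as describing interviewable attendees.
2. Pre-specify a sensitivity analysis that counts attendees not approached, or whose interview was terminated, because of intoxication as binge-positive and, in a separate analysis, as FAST-misuse-positive.
3. In that analysis, weight interviewees by the inverse of the recruitment fraction among interviewable attendees, by site and wave, using the ED attendance database. The weighting is essential, for the reason shown in the working.
4. State that mean FAST describes interviewable attendees only.

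The cost is some extra analysis and no new data, since the attendance database and the reasons for non-approach already exist. The result relies on those reasons being logged accurately and on interviewees representing other interviewable attendees within site and wave. Subgroup versions are limited to characteristics recorded without an interview.
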